### Aims and Hypotheses

MindBlooming is a two-year research project with multiple primary goals and related hypotheses. Firstly, we aim to design and implement a new Internet-Based Multi-Approach Intervention (IB-MAI) for university students. The intervention covers a wide range of mental health issues that are relevant within the university student population [11,28] and that are treatable with IBIs [23,25,29]. Furthermore, the intervention is tailored to the individual’s needs. The mental health issues that MindBlooming addresses are depression, anxiety, sleep problems, self-disruptive thoughts, job- and study-related stress and burnout, and chronic pain.

Secondary aims will be: (1) the feasibility assessment of this IB-MAI (in terms of acceptability, satisfaction, usability, and uptake) through a pilot study on a restricted sample; (2) a randomized controlled trial (RCT) to compare the IB-MAI with web-education, as the control condition (CC); and (3) exploratory analysis to tune a predictive model on the collected data adopting Machine Learning techniques.

We hypothesize that: (1) the design and implementation of the IB-MAI treatment will be feasible; (2) the majority of the students will accept and be satisfied with the treatment; (3) the IB-MAI will be superior to the CC on both the primary and secondary outcome measures; and (4) the large amount of collected data will allow the identification of predictors of treatment response and different trajectories in treatment response.

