### 2.7. Sample Size Calculation

Considering the attrition rate, we will recruit 260 students to obtain 200 study completers. A total of two-hundred participants will allow to detect an effect size of at least d = 0.40, fixing a power (1 − β) of 80%, and an alpha of 0.05 (two-tailed) in a between group comparison (e.g., comparing the two treatments). This sample size is similar to Harrer et al. [25]. The effect size is estimated considering a recent meta-analytic review for Internet-based stress interventions which reports effect sizes ranging between d = 0.32 and d = 0.64 [81].

Frequentist and Bayesian approaches have their own advantages and drawbacks in data analysis. We will adopt both to provide robust evidence to the specific statistical approach.

We conducted a Bayes Factor Design Analysis (BFDA) [82] (i.e., the counterpart of power analysis in the Bayesian world) to estimate the Bayesian analysis sensitivity, given the sample size of 200 people. We simulated 10,000 results, fixing the Bayes Factor (BF) decision boundary at 10, and an estimated effect size for a true H1 equal to d = 0.40. The BFDA simulation was performed for a default prior (i.e., a Cauchy distribution with a scale = 0.707) and an informative prior (i.e., a t distribution with μ = 0.35, df = 3, r = 0.102), considering true H0 (i.e., d = 0) and H1 (d = 0.40). Given those parameters, we estimate to surpass the decision boundary for H1 in 87.8% adopting the default prior and 93.8% of the case adopting the informed prior. In the case of a true H0, the decision boundary is surpassed in 45.5% and 62.2% of the cases adopting the default or the informed prior, respectively. The design is robust to the misleading evidence, showing a false positive evidence rate of 0.002 and 0.006 adopting the default or the informed prior. No false negative evidence has been observed over 10,000 simulations with any of the two priors. In the case of inconclusive evidence, we will increase the sample size until the BF decision boundary is surpassed (BF > 10) in either one of the two directions supporting H1 or H0.

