For what concerns the predictive model, we will explore the possibility to use ML algorithms to tune a model able to predict the responders on each of the primary outcomes starting from the socio-demographic information collected and the primary and secondary outcome measures in two steps. First, we will use only socio-demographic information to predict the primary outcome measure of each module. Second, we will use the socio-demographic information, the other primary, and all the secondary outcome measures to predict the primary outcome of each specific module. Before entering an outcome measure as a target variable (i.e., to be classified/predicted variable), variables have to be dichotomized. We will classify participants as responders or non-responders, adopting the minimum clinical importance difference and adopting a distribution approach [85]. A responder will be defined as a participant that records a change larger than 1 standard error of the mean (SEM) calculated on the baseline distribution. For example, the effectiveness of the first module is measured primarily on the BDI-II scale. We will first identify participants that change more than 1 SEM to classify responders and non-responders. Then we will use ML algorithms to predict this outcome starting from socio-demographic in a first step, and socio demographic plus the other outcome variables (except BDI-II of course) in a second step. We will test five different algorithms to have a good mixture of simple linear (LDA), nonlinear (CART, kNN), and complex nonlinear (SVM, RF) methods, thus covering the most used and diffused ML methods [86]. A total of 20% of the data will be held out for testing purposes, thus ML training will be performed on the remaining 80% data of the total sample. The portion of sample holdout will be set at the beginning and kept constant for all the algorithms tested and outcomes targeted, to make the different models’ performances directly comparable.

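### The responder cut-off for the machine-learning aim is one standard error of the mean, which measures the precision of a group average and cannot serve as a threshold for one student's change

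*Protocol article*

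**What the plan says.** Section 2.8 (Statistical Methods) describes models that predict who responds on the primary outcome of each module. Before modelling, each outcome is made binary by classifying participants "adopting the minimum clinical importance difference and adopting a distribution approach". The cut-off is then given as "a change larger than 1 standard error of the mean (SEM) calculated on the baseline distribution". The BDI-II example repeats the rule: "We will first identify participants that change more than 1 SEM to classify responders and non-responders". The resulting label is the target for all five algorithms.

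The abbreviation SEM is expanded once, as standard error of the mean, and is not redefined anywhere. The section gives no baseline SD, reliability coefficient, numerical cut-off or sign of change.

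The listed predictors are socio-demographic data in a first step, with the other primary and all secondary outcome measures added in a second. One fifth of the data is held out, "thus ML training will be performed on the remaining 80% data of the total sample".

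Under Aims and Hypotheses, the machine-learning work is called exploratory, and the fourth hypothesis expects it to allow "the identification of predictors of treatment response and different trajectories in treatment response". Section 2.7 (Sample Size Calculation) states: "Considering the attrition rate, we will recruit 260 students to obtain 200 study completers". It also lets enrolment continue past the planned number if the Bayes factor is inconclusive.

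**The concern.** The standard error of the mean, SD/√n, says how precisely a group's average is known. It carries no information about how far one student's score moves between two occasions through measurement error alone, nor about how large a change matters to that student. The usual distribution-based yardstick for an individual is the standard error of measurement, SD × √(1 − reliability), which has the same initials.

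Two consequences follow if the rule is applied as written. First, the cut-off depends on how many students enrol. Because Section 2.7 allows enrolment to grow, a student with fixed scores could move from non-responder to responder only because others joined. Second, the cut-off is so small that a large share of pure measurement noise would pass it and be reported as a minimum clinically important change. Every model for every module takes this label as its target, so the whole predictive aim inherits the problem.

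**Working it through.** **Inputs.** From Section 2.7: 260 recruited, 200 completers, d = 0.40, 80% power, two-sided alpha 0.05. From Section 2.4: two of six modules per participant. Not in the article and therefore assumed: retest reliability r of 0.7 to 0.9, normally distributed scores with equal SD at both occasions, an even spread over modules, and a BDI-II baseline SD of 8 to 12 points.

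**1. The plan's own figure.** The article gives no numerical value for the cut-off, so the figure to reproduce is the sample size on which it depends. Per arm, n = 2 × (1.960 + 0.842)² / 0.40² = 98.1, rounded up to 99, or 198 in total. This agrees with the 200 completers given for the stated aim to "detect an effect size of at least d = 0.40". Power with 100 per arm is 0.807 by the normal approximation and 0.804 by the noncentral t.

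**2. The cut-off as written**, in units of the baseline SD, is 1/√n:

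| Baseline distribution taken over | n | Cut-off (SD) |
|---|---|---|
| All recruited | 260 | 0.062 |
| Completers | 200 | 0.071 |
| Recruited and given one module (260 × 2/6, even split assumed) | about 87 | 0.107 |

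With a BDI-II SD of 8 to 12, the cut-off at n = 200 is 8/√200 = 0.57 to 12/√200 = 0.85 points. If the scale is scored in whole points, any one-point improvement passes.

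**3. How often noise alone passes.** With no true change, the difference between two scores has SD √(2(1 − r)) in baseline SD units. The chance of an apparent improvement beyond cut-off t is 1 − Φ(t / √(2(1 − r))). For one standard error of measurement, t = √(1 − r), so the ratio inside Φ is 1/√2 = 0.707 whatever r is, and the chance is 0.240.

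| | r = 0.7 | r = 0.8 | r = 0.9 |
|---|---|---|---|
| SD of change under no true change | 0.775 | 0.632 | 0.447 |
| P(improvement beyond cut-off), n = 260 | 0.468 | 0.461 | 0.445 |
| P(improvement beyond cut-off), n = 200 | 0.464 | 0.455 | 0.437 |
| P(improvement beyond cut-off), n = 87 | 0.445 | 0.433 | 0.405 |
| One standard error of measurement (SD) | 0.548 | 0.447 | 0.316 |
| P(improvement beyond it) | 0.240 | 0.240 | 0.240 |
| Its ratio to 0.071 SD | 7.7 | 6.3 | 4.5 |

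**4. What signal remains.** Suppose the true mean improvement is 0.40 SD. The chance of passing is then 1 − Φ((t − 0.40) / √(2(1 − r))). At r = 0.8 and n = 200 this is 0.699 with the cut-off as written, against 0.455 with no true change. With one standard error of measurement it is 0.470 against 0.240.

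**The case against.** The strongest reply is that this is a slip of terminology. The sentence speaks of a minimum important difference and a distribution-based approach, and the standard error of measurement fits that description. That may well be so. The cited source is not available here, so intent cannot be settled. The text nevertheless spells out mean and ties it to the baseline distribution, and an analyst following it would compute SD/√n. A probable slip makes the repair easy, but the rule still needs repair. Nor can it be set aside as a detail that a condensed article leaves out, because the article states the rule.

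It is also fair to say that the consequence is contained. The label is used only in the exploratory modelling. The t-tests, the mixed ANOVA and the sample size do not depend on it.

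A reader might infer three stronger points that the article does not support:

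- **The label is worthless.** It is not. Step 4 shows about 70% labelled with a true gain of 0.40 SD, against 46% with none. It behaves like any improvement versus none, which is noisy but not empty.
- **Students who get worse count as responders.** The rule gives no sign, and a two-sided reading would double the no-change figures to 87–93%. But the word responder and the link to module effectiveness make improvement the natural reading, so those figures are not a fair measure of the plan. The sign should still be written, because the primary outcomes in Section 2.6.1 include both symptom scales and a quality-of-life scale.
- **The models pool both arms, so they cannot find predictors of treatment response.** The sentence on the hold-out refers to the total sample but does not mention the arms, and only the intervention arm receives modules. Pooling is a plausible reading, not an established fact. What can be said is that arm is absent from the listed predictors and that the article does not say whether control participants are included.

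**Conclusion.** The point holds for the rule as written. The cut-off is the wrong quantity for classifying individuals. It varies with enrolment from 0.062 to about 0.11 SD over the plausible bases, and at n = 200 it labels about 44–46% of unchanged students as responders, against 24% with one standard error of measurement. These percentages rest on the assumed reliability of 0.7 to 0.9 and on normality. Taking the baseline distribution over 260 or about 87 students widens the range only to about 40–47%.

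The replacement should not be oversold. At r = 0.8, the gap between students with a 0.40 SD gain and those with none is similar under both rules: 0.699 − 0.455 = 0.244 and 0.470 − 0.240 = 0.230. The gain is that false responders among the unchanged fall by nearly half, that the ratio of the two rates rises from 1.54 to 1.96, and that the cut-off no longer moves with n. The damage is confined to the exploratory predictive aim and the fourth hypothesis, where results would be presented as clinically important response when the label does not carry that meaning.

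**What to change.** In Section 2.8, define a responder as a participant whose score improves from T0 to T1, in the beneficial direction stated for each scale, by more than one standard error of measurement, SD_baseline × √(1 − reliability). Fix the reliability value and its source for each scale before any labels are computed, and use the same term in the BDI-II example.

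As a secondary clarification, state whether control participants enter the models. If they do, add arm to the predictors. If only the intervention arm is used, say so, and note that such a model predicts improvement under the intervention without separating it from natural recovery.

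The cost is a few sentences and one reliability value per scale. Fewer participants will be labelled responders: in the illustration at r = 0.8 with a 0.40 SD gain, 47% instead of 70%. A model restricted to the intervention arm would also have a smaller training set. Recruitment, the efficacy analyses and the sample size need no change.

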### 2.1. Participants and Recruitment

University students aged between 18 and 29 will be invited to participate; to be included, they must declare to have experienced at least mild- or moderate-intensity forms of mental health symptoms (no specific diagnostic screening will be performed in this phase), and they must not currently be in psychotherapy or start psychotherapy during the entire duration of the treatment. Participants are also required to have a phone based on Android or iOS operating systems and an Internet connection. Exclusion criteria include the inability to communicate in Italian.

Participants will be recruited through social networks (e.g., Facebook and Instagram), students’ WhatsApp groups (to include students not using the mentioned social networks, thus avoiding selection biases), and the Sona System recruitment platform made available by the University of Milan-Bicocca. Moreover, to further encourage participation, posters will be placed in local universities. In this phase they will receive preliminary information. Then, through a web link, they will be redirected to a specific landing page with more detailed information about the mobile app. On this web page, participants will be redirected to the proper marketplace (Apple Store and Google Play) to download the app on their smartphones. If possible, European Credit Transfer and Accumulation System (ECTS) credits will be awarded to participants. Once their eligibility has been verified and they have signed an online informed consent form, students interested in participating will be included in the study. We will collect the information concerning the diverse participants’ recruitment channels to ensure that there is no difference in baseline data among different recruitment channels. The same standards for data collection will be applied through different channels.

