### 2.4. Intervention

MindBlooming is conceived as an Internet-Based Multi-Approach Intervention (IB-MAI) intended to provide psychoeducation and teach new strategies to cope with different psychological problems. We consider MindBlooming to be multi-approach since it integrates different psychotherapeutic strategies such as Cognitive Behavioral Therapy [35], Acceptance and Commitment Therapy [36], Mindfulness-Based Cognitive Therapy (MBCT) [37,38], Mindfulness-Based Stress Reduction (MBSR) [39], and Dialectical Behavioral Therapy [40]. All these interventions are evidence-based and several studies proved their efficacy in treating different psychological conditions (for an overview, see [41] and APA division 12 list of research-supported psychological treatments, https://div12.org/psychological-treatments/, accessed date 29 December 2021). The intervention consists of 6 interactive modules: depression, anxiety, sleep problems, self-disruptive thoughts, job- and study-related stress and burnout, and chronic pain. A total of two modules will be assigned to each participant based on the initial screening and specific requests and preferences. In addition to the assigned treatments based on the initial screening, all participants will receive a separate training to improve their relational and empathy skills: during the 6th week, they will have access to two videos focused on the importance of relationships on our health, social support as a protective factor, social isolation and loneliness as a risk factor, emotion regulation, and empathy. Afterward, they will have access to a set of exercises, including quizzes about social relationships, assertive communication training, DBT [40], and Interpersonal Psychotherapy (IPT) for Depression strategies (which correlate depressive symptomatology to relational problems) [42]. Moreover, during the 7th week of treatment, more contents in the same formats (videos, texts, and quizzes) will be proposed, focusing on emotions and relationships problems related to the specific issues faced in the assigned modules (e.g., problems in relationships in association with depressive symptoms).

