#### 2.6.2. Secondary Outcome Measures

❖Visual Analogue Scales (VAS) for psychological and physical pain (6 items) [32].❖Insomnia Severity Index (ISI) to investigate the impact of insomnia in the last two weeks (7 items) [74].❖Toronto Alexithymia Scale (TAS-20), consisting of 20 items investigating levels of alexithymia [75,76].❖Coping Orientation to the Problems Experienced (COPE-NVI-25) [77,78], consisting of 25 items investigating coping strategies.❖Life Events Checklist (LEC) [79], composed of 16 items investigating the subject’s stressful experiences.❖Reasons for Living Inventory (RFLI) [80], consisting of 48 items investigating the subject’s reasons for living.❖COVID-19-related questions compiled according to the International Association for Suicide Prevention (IASP) guidelines for suicide prevention research [56].

Given the feasibility nature of this study, data on the program’s acceptability will also be collected at post-treatment (T1) through the same measures used in the pilot study and described in the related paragraph.

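### The responder label in 2.8 has no baseline condition and no direction of change, so on scales where many students start near the best score it mixes absence of the problem with non-response

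*Protocol article*

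**What the plan says.** Protocol article, 2.8 (Statistical Methods) sets out the label, the targets and the data split.

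- **Label:** the rule reads "A responder will be defined as a participant that records a change larger than 1 standard error of the mean (SEM) calculated on the baseline" (that is, on the spread of scores at T0). The worked example for the depression scale repeats the rule: "We will first identify participants that change more than 1 SEM to classify responders and non-responders". Neither sentence gives a direction or a starting score.
- **Targets:** the models are to "predict the responders on each of the primary outcomes".
- **Data:** 20% is held out and "ML training will be performed on the remaining 80% data of the total sample". The holdout is set once and kept the same for all algorithms and outcomes.
- **Predictors:** step 1 uses socio-demographic data. Step 2 adds the other primary scales and all secondary scales; the target scale is left out.

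Three other sections determine who is labelled.

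- **2.1, entry:** "they must declare to have experienced at least mild- or moderate-intensity forms of mental health symptoms". No scale has a minimum score.
- **2.4, treatment:** "A total of two modules will be assigned to each participant based on the initial screening and specific requests and preferences". There are six modules.
- **2.6, assessment:** every participant completes the full battery of primary and secondary measures.

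**The concern.** A model of treatment response should separate students who had a problem and improved from students who had it and did not. Under the rule as worded, a student with no pain at T0 and none at T1 has zero change, does not pass the threshold, and becomes a non-responder on the pain scale. That student says nothing about response.

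Leaving the target scale out of the predictors does not cure this, because related measures stay in at step 2: the physical-pain VAS for the pain inventory, the insomnia index for the sleep-quality index, and the reasons-for-living inventory for the suicide-risk scale. A model can discriminate the label by recognising who has the problem. The fourth hypothesis, that predictors of treatment response will be identified, could then appear supported when nothing predicts response.

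**Working it through.** **The plan's own figure.** The responder rule has no stated figure. The only number used from the plan is the sample size in 2.7, which reproduces: 2 × (1.960 + 0.842)² / 0.40² = 98.1, so 99 per arm and 198 in total, against 200 completers stated. Recruiting 260 implies attrition of 1 − 200/260 = 23.1%.

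**Step 1. Size of the threshold.** Read literally, it is SD/√N. The article gives no baseline SD, so I assume 5 to 12, with N from 200 to 260:

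- smallest: 5/√260 = 0.31 points
- largest: 12/√200 = 0.85 points

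A one-point change on an integer score therefore passes. With no direction stated, a one-point worsening passes too.

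**Step 2. Students at the best score.** Assumptions: a share z is at the best score at T0 and stays there; the rest respond with probability r = 0.5, unrelated to any predictor.

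- Non-responders = 1 − (1 − z)r
- Share of non-responders who never had the problem, s = z / [1 − (1 − z)r]
- AUC of a has-the-problem flag = 0.5 × (1 + s)

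| z | s | AUC of flag | AUC of flag, r = 0.4 to 0.6 |
|---|---|---|---|
| 30% | 0.30/0.65 = 46% | 0.73 | 0.71–0.76 |
| 50% | 0.50/0.75 = 67% | 0.83 | 0.81–0.86 |
| 70% | 0.70/0.85 = 82% | 0.91 | 0.90–0.93 |
| 85% | 0.85/0.925 = 92% | 0.96 | 0.95–0.97 |

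Among students able to improve, the true AUC is 0.50 by construction. A real predictor would be a noisy proxy and not a perfect flag. With a correlation of 0.7 with severity, simulated AUCs are about 0.64, 0.71, 0.78 and 0.86. These depend on the severity distribution assumed; other choices gave 0.63–0.66 at z = 30% and 0.80–0.83 at z = 85%.

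**Step 3. Unaffected students low but above the floor.** This is a simulated scale floored at zero. Between 20% and 80% have the problem, with a mean improvement of 4 points among them; unaffected students have a mean score of 5 and no true mean change.

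- With the literal threshold, 42–43% of unaffected students are labelled responders if improvement is required, and 84% if any change counts.
- With a threshold based on the standard error of measurement (reliability 0.9 assumed), these become 26% and 53%.
- The AUC of the flag is 0.59 to 0.67.

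In the same simulation with unaffected students at zero, none is a responder and the AUC is 0.67 to 0.97.

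**Step 4. Accuracy.** With r = 0.5 the flag classifies correctly a share z + 0.5(1 − z). Always guessing non-responder is correct for 1 − 0.5(1 − z), which is the same number (85% at z = 70%). High accuracy here would reflect class imbalance; the artefact shows in discrimination.

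**The case against.** **The analysis set per target is not stated.** Section 2.8 describes the models module by module, so each could be meant for the students assigned that module, and the total-sample wording may describe only the split. A single split is compatible with later subsetting. This stands in part: labelling everyone is an inference. It is a strong one, because the rule speaks of participants without restriction, everyone completes every scale, and one holdout serves all outcomes.

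**A reader might infer that every student without a given problem cannot improve and is therefore counted as a non-responder, on every scale.** The documents do not support that. Only students at or near the best score lack room to improve. Low scorers on scales such as the depression or anxiety inventory can pass a sub-one-point threshold in either direction, so the mislabelling runs both ways (step 3). The article gives no reason to expect clustering at the floor beyond, plausibly, the pain and suicide-risk scales.

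**The sizes are assumed.** This stands. Prevalence, response rate and proxy strength have no source in the article, and the article names no performance measure; AUC is my choice.

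**The aim is exploratory and hypothesis 4 has no success criterion.** This is also true, and it limits the importance of the point. It does not make the label correct. Nor is this detail merely left to a fuller plan: the article itself fixes the label, the split and the predictors.

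**Conclusion.** The point holds in limited form. As worded, the label has neither a baseline condition nor a direction, and the text points to its use for all participants on all primary scales. Where many students start at or near the best score, the label partly records whether the problem was present, and correlated step 2 predictors can exploit this. The flag's AUC is 0.73 to 0.96 under 30% to 85% at the floor with 50% random response, and about 0.59 to 0.67 where unaffected students sit above the floor. These figures show the mechanism over a range and do not forecast this trial's results. The between-group comparison is untouched. The change should be made, but the trial's main conclusions do not depend on it.

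**What to change.** In 2.8:

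1. Define response as improvement beyond the threshold, with the improving direction stated for each scale.
2. Label, train and test each target only among participants who had that problem at T0 or who were assigned that problem area at screening. Having the problem means a pre-set baseline score on that scale that at least leaves room to exceed the threshold. Screening identifies areas of distress in both arms (2.4 and 2.5). Quality of life has no module of its own, so it needs the baseline-score route.
3. Set the label to missing for everyone else.
4. Keep the one fixed holdout and subset within it.
5. Report the number labelled on each scale.

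Requiring only room to reach the threshold would not be enough. With a threshold below one point, it removes only students exactly at the best score.

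The cost is analysis wording and no new data, but smaller sets. If the six areas were equally common and two were identified per student in both arms (an assumption), about 200 × 2/6 = 67 completers would remain per target, about 33 of them in the intervention arm. The 20% test set would fall from 40 to about 13. Performance figures will look less favourable, and some targets may prove too small to model.

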### 2.6. Outcome Measures

Participants will be screened with a complete online battery to assess their symptoms, including both primary and secondary outcome measures, at pretreatment baseline (T0), after the 7-week IB-MAI treatment, or CC completion (T1), at 12-week follow-up (T2), and 24-week follow-up (T3) (see Figures S1 and S2 for the study design and assessments). Moreover, at pretreatment time (T0), socio-demographic questions are included; these concern marital status, educational qualification, employment status, physical or psychiatric illnesses, and past or current therapies. Questions related to gender and the COVID-19 pandemic are included to investigate the influence of the pandemic on students’ mental health status. These items were drawn up according to the International COVID-19 Suicide Prevention Research Collaboration guidelines [56]. In contrast, those relating to gender were taken from the Williams Institute of the UCLA School of Law for health surveys [57].

Since participants have a timeframe to begin and complete each week of treatment, the overall treatment duration can differ among subjects. Therefore, post-treatment and follow-up time points will be calculated for each participant, starting from the end of the last activity.

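### The step-2 response models exclude the target scale's own baseline score, so correlated scales can appear as response predictors by standing in for baseline severity

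*Protocol article*

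**What the plan says.** The aim appears in Aims and Hypotheses as "exploratory analysis to tune a predictive model on the collected data adopting Machine Learning techniques". The fourth hypothesis there expects that "the large amount of collected data will allow the identification of predictors of treatment response and different trajectories in treatment response".

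Section 2.8 (Statistical Methods) defines the variable to be predicted: "A responder will be defined as a participant that records a change larger than 1 standard error of the mean (SEM) calculated on the baseline". It sets the predictors in two steps. Step 1 uses socio-demographic data only. Step 2 adds "the other primary, and all the secondary outcome measures to predict the primary outcome of each specific module". The worked example for the depression module repeats the rule: "socio demographic plus the other outcome variables (except BDI-II of course) in a second step".

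Section 2.6 (Outcome Measures) describes the source of these variables: "Participants will be screened with a complete online battery to assess their symptoms, including both primary and secondary outcome measures". The battery is given at T0, T1, T2 and T3. Neither Section 2.8 nor the machine-learning paragraph of Section 2.7 gives the time point of the step-2 predictors. Nothing elsewhere in the article brings the target scale's T0 score back in.

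**The concern.** The exclusion seems meant to stop the model from predicting a scale from itself. That reason applies to the target's post-baseline values, which determine the response. It does not apply to the T0 score, which is available before treatment like any other baseline variable.

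Change from baseline depends on the baseline value whenever the T0-T1 correlation is below 1: on average, people who score high at T0 fall more. If the T0 score is kept out, that dependence remains and passes to whatever correlates with the T0 score. The battery offers such stand-ins. The Insomnia Severity Index, for example, stays in as a predictor when the Pittsburgh Sleep Quality Index is the target.

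Hypothesis 4 is what is at stake. A gain from step 1 to step 2 could be credited to coping, alexithymia or emotion regulation when it reflects only how severe the participant was at entry.

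**Working it through.** **The plan's own figures.** The article states no performance figure for the predictive models. Its frequentist sample size does reproduce: 2 × (1.960 + 0.842)² / 0.40² gives 99 per arm, 198 in total, against the stated 200. It is used here only to express the responder threshold: 1 SEM = SD/√200 = 0.071 SD.

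**Why T0 predicts change.** With equal variances at T0 and T1 and observed correlation r, the correlation of T0 with improvement is √((1 − r)/2). A second scale that correlates c with T0, and is related to T1 only through T0, has correlation c × √((1 − r)/2) with improvement. With assumed r = 0.6 and c = 0.6:

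- target T0: √(0.4/2) = 0.45
- pure proxy: 0.6 × 0.45 = 0.27

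A simulation with these values, adding a difference in mean improvement between arms, gave 0.44 and 0.26, with AUCs of 0.70 and 0.62.

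**Simulation with measurement error.** There were 400,000 draws. All inputs are assumptions, because the documents give none: target reliability 0.9; mean improvement 0.4 SD; true severity correlating ρ between T0 and T1 (observed correlation 0.9ρ); and a proxy scale correlating c with the target at T0, with no effect of its own on response. Coefficients are changes in response probability per SD of the proxy, from a linear model.

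| ρ | c | AUC, target T0 | AUC, proxy T0 | AUC, proxy T0 + T1 | Proxy coefficient, target T0 omitted | Proxy coefficient, target T0 included |
|---|---|---|---|---|---|---|
| 0.5 | 0.5 | 0.74 | 0.61 | 0.67 | +0.091 | −0.012 |
| 0.5 | 0.7 | 0.74 | 0.65 | 0.76 | +0.127 | −0.025 |
| 0.7 | 0.5 | 0.70 | 0.58 | 0.63 | +0.066 | −0.019 |
| 0.7 | 0.7 | 0.70 | 0.61 | 0.71 | +0.091 | −0.041 |
| 0.9 | 0.5 | 0.65 | 0.54 | 0.56 | +0.028 | −0.034 |
| 0.9 | 0.7 | 0.64 | 0.55 | 0.61 | +0.040 | −0.069 |
| 1.0 | 0.5 | 0.61 | 0.50 | 0.50 | 0.000 | −0.045 |
| 1.0 | 0.7 | 0.61 | 0.50 | 0.50 | +0.001 | −0.093 |

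Replacing the threshold by a standard error of measurement, SD × √(1 − 0.9) = 0.32 SD, moves the AUCs by no more than 0.01. The last column then reaches −0.081 at ρ = 0.9 and −0.122 at ρ = 1.0.

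**Reading the table.** For ρ from 0.5 to 0.9 the proxy reaches an AUC of 0.54 to 0.65 without any effect of its own. Its positive coefficient disappears once target T0 is in the model. The negative remainder comes from measurement error in T0. On the change scale the adjusted coefficient is −cρ(1 − reliability)/(1 − c²), which is zero when reliability is 1. With ρ = 0.9, c = 0.7 and reliability 0.9 it is −0.7 × 0.9 × 0.1/0.51 = −0.12 SD.

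**The case against.** The best defence is that leaving the target scale out is a choice, not a slip. The T0 score is arithmetically part of the change score, so its predictive value is largely regression to the mean. In the simulations every participant has the same expected benefit, so its AUC of 0.60 to 0.74 says nothing about who benefits from the intervention. Asking what demographics and other scales predict is a coherent exploratory question, and a proxy is a legitimate input to a purely predictive model.

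Part of this stands: accuracy gained from target T0 should not be read as evidence of differential benefit. But the exclusion does not remove regression to the mean from the model. The correlated scales bring it in unlabelled, whereas including T0 makes it visible. The stated purpose is also to identify predictors, not only to forecast.

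A reader might infer that T1 to T3 values of the other scales will be used and will leak the outcome. The text does not say so. It gives no time point, the word predict is reasonably read as meaning baseline data, and a condensed article may leave this detail to the full plan. The T0 + T1 column shows what would happen if they were used (AUC 0.02 to 0.11 higher for ρ of 0.5 to 0.9), not what is planned.

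**Conclusion.** The point holds for the target scale's T0 score. Its exclusion is stated both as a general rule and in the worked example, and nothing in the article reverses it. Correlated scales can therefore appear as predictors of response partly or wholly as proxies for baseline severity.

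It would go too far to say that proxies will be reported as predictors. The size rests on assumed correlations: proxy AUC is about 0.54 to 0.65 for ρ from 0.5 to 0.9, and 0.50 if true severity is perfectly stable apart from a uniform shift. The missing T0 restriction is a matter for clarification, not an error.

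The analysis is labelled exploratory. The comparisons of the two arms, the sample size and the efficacy conclusion are untouched. The rule is still worth changing, because it weakens hypothesis 4 and the correction needs no new data.

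**What to change.** In Section 2.8, state that step 2 includes the target scale's T0 score and excludes only its T1 to T3 values. Report what the other scales add over a model with socio-demographic data plus target T0. In the same sentence, confirm that every predictor is a T0 value.

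The cost is one sentence of wording and one extra comparison model per target; the data are already being collected. The other scales will look less predictive. Because T0 is measured with error, an artefact of opposite sign can remain. It is small in absolute terms for ρ up to 0.9 (at most about 0.08 in response probability per SD), but when severity is very stable it can match or exceed the one removed. Small negative associations after adjustment should therefore not be interpreted either.
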